## Abstract

**Background:**

Screening for abdominal aortic aneurysm (AAA) of men aged 65-74 years reduces the AAA-related mortality and is generally considered cost effective. Despite of this only a few national health care services have implemented permanent programs.

Around 10% of men in this group have peripheral arterial disease (PAD) defined by an ankle brachial systolic blood pressure index (ABI) below 0.9 resulting in an increased mortality-rate of 25-30%. In addition well-documented health benefits may be achieved through primary prophylaxis by initiating systematic cholesterol-lowering, smoking cessation, low-dose acetylsalicylic acid (aspirins), exercise, a healthy diet and blood-pressure control altogether reducing the increased risks for cardiovascular disease by at least 20-25%.

The benefits of combining screening for AAA and PAD seem evident; yet they remain to be established. The objective of this study is to assess the efficacy and the cost-effectiveness of a combined screening program for AAA, PAD and hypertension.

**Methods:**

The Viborg Vascular (VIVA) screening trial is a randomized, clinically controlled study designed to evaluate the benefits of vascular screening and modern vascular prophylaxis in a population of 50,000 men aged 65-74 years. Enrolment started October 2008 and is expected to stop in October 2010. The primary outcome is all-cause mortality. The secondary outcomes are cardiovascular mortality, AAA-related mortality, hospital services related to cardiovascular conditions, prevalence of AAA, PAD and potentially undiagnosed hypertension, health-related quality of life and cost effectiveness. Data analysis by intention to treat.

**Results:**

Major follow-up will be performed at 3, 5 and 10 years and final study result after 15 years.

**Trial registration:**

ClinicalTrials.gov NCT00662480

## Background

It has been demonstrated that abdominal aortic aneurysm (AAA) screening of men aged 65-74 years reduces AAA mortality. Research at Viborg Hospital published in the British Medical Journal in March 2005 [1] shows that only 352 Danish men above the age of 65 require AAA screening to avoid one AAA rupture-related death in the subsequent 5-year period. Furthermore, it seems that the long-term economic efficiency of screening is at a level, which is generally considered cost effective, at least from a health care sector perspective [2-4]. Despite the clinical and economic evidence for the attractiveness of population screening, few national health care services have implemented permanent programs.

The majority of AAAs diagnosed by screening does not comprise a rupture risk due to being detected early, but nearly half expand to sizes requiring repair. However growth may be limited through smoking cessation [5,6], low-dose aspirin [7-9], statin treatment [10] and ACE inhibitor therapy [11] which will ultimately also reduce the increased cardiovascular risk of the affected patients [12].

International studies indicate that approximately 5-10% of men above the age of 60 show signs of peripheral arterial disease (PAD; ankle brachial systolic blood pressure index (ABI) <0.9) - a proportion which increases with age, and mainly non-symptomatic. Approximately 25-30% of these men will die from cardiovascular disease within a 5-year period, and an even higher proportion will need hospitalization due to cardiovascular disease. Cholesterol-lowering, smoking cessation, low-dose acetylsalicylic acid (aspirins), exercise, a healthy diet and blood-pressure control reduce the increased risks for cardiovascular disease by at least 20-25% [13-16]. So far, screening studies have neglected the interaction between PAD-screening and such general prophylactic efforts, and thus the benefit and cost effectiveness of screening may be underestimated.

In sum, well-documented health benefits may be achieved through prophylactic screening for cardiovascular disease. Advantages include fewer premature deaths and a reduction in the number of amputations and hospital admissions. Furthermore, hospital costs may be reduced by the decrease in admissions and in-hospital post-operative care.

The benefits of combining screening for AAA and PAD thus seem evident; yet they remain to be established. The objective of this study is to assess the efficacy and the cost-effectiveness of a combined screening program for AAA, PAD and hypertension.

## Methods

### The Viborg Vascular screening program

In the timeframe of October 2008 until October 2010 approximately 50,000 65-74 year-old Danish men will be randomized to either receive an invitation for vascular screening or being a control (Figure 1). ABI measurement, ultrasound scan of the aorta in addition to a questionnaire regarding lifestyle parameters, medical and smoking status is performed by trained project-nurses in 3 mobile units at local hospitals in the mid region of Jutland, Denmark.

**Figure 1 F1:**
[figure not shown]
**Expected flow-chart concerning vascular screening (VIVA) for peripheral arterial disease, abdominal aortic aneurysm and hypertension**.

In the case of infrarenal aortic dilatation such findings are; i) pre-aneurysmatic (<24-30 mm<) or ii) aneurysmatic (≥30 mm). Dilatation <50 mm is controlled annually with ultrasound scanning and dilatation > 50 mm referred for consultation by a vascular surgeon. PAD may be reliable diagnosed with a portable ultrasound Doppler and blood pressure cuff. PAD is defined as ABI below 0.9 or above 1.4 and annual control is offered. In the case of suspected undiscovered hypertension (bloodpressure > 160/100) the patient is encouraged to see his family physician for further assessment and treatment.

During a training course, six project-nurses have been educated in the natural history of AAA, PAD and hypertension, instruction in life style changes and smoking cessation, blood sampling and bed side cholesterol measurement and the initiation of antiplatelet and lipid lowering medication. They were trained under supervision to measure ABI and perform ultrasound scanning of the aorta Independent examinations were only allowed, when the team-interobserver variation of aortic anterior-posterior diameter were below 2 mm, and ABI below 10%. The nurses operate in three mobile teams which will each be equipped with uniform portable Dopplers, blood pressure cuffs and portable ultrasound scanners and perform the screening sessions at the hospitals in the region. The project secretary will continually invite participants to their regional hospital using the names and address information from the randomization files.

Participants are informed that they should wear expedient footwear. The letter is accompanied by an option to refuse or reschedule in writing. Non-responders are re-invited once. Finally, enclosed with the invitation is a small questionnaire on smoking habits, anamnesis, walking-related pain (Walking Impairment Questionnaire), use of medicine, and the EUROQOL five dimensions (EQ5D) health questionnaire to obtain psychometric measures. This has recently been validated in Danish population norms [17]. Study participants commit to the program with a written consent using pre-printed consent forms.

To visualise the aorta the ultrasound 4 MHz transducer is placed longitudinally just above and a little to the left of the navel. In cases of dilation, the maximal perpendicular AP diameter is measured. If no dilation is found, the AP diameter is measured two centimetres above the bifurcation. Simultaneously, peripheral pulse data are recorded by the other nurse. Brachial blood pressure is automatically measured concurrently with the ankle blood pressure by detecting the Doppler signal from the dorsalis pedis artery (DPA) and first inflating the blood pressure cuff until the signal disappears and then deflating the cuff until the signal reappears. The mean pressure of the two measurements is recorded, and the same procedure performed for the tibialis posterior artery (TPA). Subsequently, the same procedure is repeated in the opposite extremity.

### Follow-up and data collection

All positive findings are subject to clinical monitoring to provide a reassuring context for the communication of the finding and its consequences. In the case of PAD the participant is informed of the relatively positive prognosis of leg survival and the need to initiate suitable prophylactic measures including walking/exercise, smoking cessation, low-fat diet, aspirin and statin treatment. Cholesterol levels are measured. If it exceeds 4.0 mmol/l, cholesterol is unlikely to fall below 3.5 mmol/l following relevant diet changes and, consequently, the patient is given a prescription for 40 mg simvastatin/day. Annual follow-up with ABI measurement is offered. The EQ-5D is fulfilled upon visit and in connection with any follow-up.

In the case of AAA the aorta is reassessed, the finding is stored digitally and the calcification degree and mural thrombus is determined. Information regarding the natural history of AAA is delivered and the need to initiate suitable prophylactic measures including exercise, smoking cessation, low-fat diet, aspirin and statin treatment in accordance with the guideline from the European Society of Cardiology 2007. If the AAA exceeds a diametre of ≥ 50 mm, the patient is referred for CT scan and assessment by a vascular surgeon to further surveillance or surgery. If the AAA is below 5 cm, annual control with ultrasound scan is offered. The EQ-5D is fulfilled upon visit and in connection with any follow-up, as well as annually after AAA surgery.

Data from the screening procedure are collected in a large database. Information concerning deaths, including-date and cause of death, is obtained from the Civil Registration System. Information on visits to outpatient clinics and hospital admissions caused by cardiovascular conditions including amputations is obtained from the National Patient Registry. From the Danish Causes of Death Registry, data on cause of death are collected. The information is classified according to cause; AAA-related or cardiovascular.

### Study population

To maximize the possibility of detecting an effect, men aged 65-74 are screened, as this group has a high prevalence of non-symptomatic cardiovascular disease as well as a long remaining life expectancy. Screening of men above the age of 74 presumably would have resulted in higher prevalences of AAA and PAD, but also a higher mortality associated with other conditions and a lower acceptance rate. Similarly, screening of men below the age of 65 would demonstrate lower mortality, but also a lower prevalence and a lower rupture frequency. Among women in the age interval of 65-74, PAD and AAA frequencies are reported to be lower and to occur later in life; hence screening women would, ceteris paribus, yield a lower detection rate. Furthermore, as mortality from other causes is even higher among women as compared to men, the effect of detecting a case would be inferior. It should be noted however that the reports of such differences between genders are old and the extent to which significant differences persist is uncertain.

As per January 1, 2007 there were approximately 50,000 men aged 65-74 years in the Mid Region of Denmark, which is located from coast to coast in the middle of Jutland. This population comprise the target group for the study which has no exclusion criteria.

### Randomization

Civil registration numbers and patient data are obtained from national registries. Randomisation is stratified by municipalities, as the prevalences of the diseases are expected to differ in this relatively large region. The Region consists of 19 counties covering more than 13,000 km2, which includes some of the largest Danish cities in the eastern part, as well as rural areas in the western part of the region. The stratification furthermore ensures a minimum of time span between randomisation and invitation as local screening units individually can report back to the central randomisation office about their time schedule.

Person-data are imported to Epidata and Epi-info 6, where randomisation occurs by giving each subject a random number from 1-100, persons with a number above 51 are allocated to the intervention arm i.e. half of subjects are invited to participate in screening and half of subjects act as controls (as no permanent screening programme exists in Denmark).

### Outcome

The primary outcome variable is all-cause mortality. The secondary outcome variables are cardiovascular mortality, AAA-related mortality, hospital services related to cardiovascular conditions and costs for such services, quality of life, and aneurismal progression. Major follow-up is planned after 3, 5 and 10 years. All-cause mortality, health care-related costs, cardiovascular and AAA-related mortality and cardiovascular hospital service are compared for the two groups.

### Analysis of efficacy

Statistical analysis will be performed on an intention to treat basis. Risk ratios for all-cause mortality, cardiovascular mortality, AAA-related mortality and first cardiovascular event in the two groups will be estimated by Cox-regression. In addition, the numbers of hospital services related to cardiovascular conditions will be compared between the two groups by student's t-test. Quality of life between controls, non-attenders, attenders without positive finding, and attenderswith AAA or PAD will be compared at baseline univariately and multivariately adjusted for age, civil status and co-morbidity, and prospective data from baseline, after 3, 5 and 10 years will be compared by MANOVA. Aneurysmal progression (growth rate) will be transformed by the natural logarithm and evaluated in subgroups by univariate and multivariate linear regression analysis. SPSS 15.0, STATA 12.0 and PEPI will be used for the analysis.

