### Analysis of cost-effectiveness

The program cost per invited will be estimated using a micro-costing approach for the intervention (invitations, screenings, follow up scans). Relevant resource utilization at hospitals (surgical procedures, admissions, outpatient visits etc.) will be extracted from the National Patient Registry and valued using tariffs of the Diagnosis-Related Grouping (DRG) case-mix system. Participants' time and transportation costs will be estimated from a prospective within-sample study of about 1,000 participants using a questionnaire.

Health-related quality-adjusted life will be estimated for each individual assuming that baseline quality of life follows that of an age- and sex-matched population norm [17]. For persons detected with and/or treated for cardiovascular disease estimates of decrements in quality of life will be adapted from the literature and applied.

The net present values of costs, life years gained and QALYs gained will be compared between randomization groups [18]. The incremental ratios of costs per life-year gained and costs per quality-adjusted life year (QALY) gained will be estimated using nonparametric bootstrapping; for their interpretation the net benefit framework will be used to present cost-effectiveness acceptability curves [19,20].

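### The comparison of cardiovascular hospital-service counts is fixed as an unadjusted t-test; adjusting for each man's earlier use in the same registry would be a cheap gain in precision

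*Protocol article*

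**What the plan says.** Cardiovascular hospital services are a secondary outcome, to be compared between the randomised groups (Outcome). The method is fixed under Analysis of efficacy: "the numbers of hospital services related to cardiovascular conditions will be compared between the two groups by student's t-test". No covariate is named, and the test admits none. The same paragraph does name covariates for another outcome: baseline quality of life is also to be compared "multivariately adjusted for age, civil status and co-morbidity".

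The source of the counts is given under Follow-up and data collection: "Information on visits to outpatient clinics and hospital admissions caused by cardiovascular conditions including amputations is obtained from the National Patient Registry". The cost analysis uses the same registry: "Relevant resource utilization at hospitals (surgical procedures, admissions, outpatient visits etc.) will be extracted from the National Patient Registry". Its comparison is described only in general terms: "The net present values of costs, life years gained and QALYs gained will be compared between randomization groups". The ratios, including "costs per quality-adjusted life year (QALY) gained will be estimated using nonparametric bootstrapping", carry no statement on baseline adjustment either way.

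Two further statements bear on the point. Under Study population: "This population comprise the target group for the study which has no exclusion criteria". Under Randomization: "Civil registration numbers and patient data are obtained from national registries".

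**The concern.** With no exclusion criteria, men with established cardiovascular disease will be in both arms. It is reasonable to expect that men who used cardiovascular hospital services before randomisation will tend to use them afterwards. A two-sample t-test leaves that persistent variation between men in the error term. A regression that includes each man's earlier use removes part of it.

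Precision matters because the expected contrast is diluted. On the article's own planning figures (Power and expected benefit), at most 4% + 8% = 12% of men have an abdominal aortic aneurysm or peripheral arterial disease, and 75% attend. So at most 0.75 × 12% = 9% of invited men have such a finding. Medication can be started in one-third of them, about 3% of those invited. Referral for suspected hypertension comes on top and is not quantified. Any difference in mean counts between the arms is therefore spread over many men for whom the detection of these two conditions changes nothing.

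**Working it through.** **Inputs from the article.** Outcome: number of cardiovascular hospital services per man, from the National Patient Registry. Method: Student's t-test, no covariate. Planned arm size: 23,604. That figure was derived for mortality and is used here only as a sample size. The article states no mean, standard deviation, power or precision for the counts or the costs, so there is no figure of its own to reproduce.

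**Assumed input.** r, the correlation within arm between cardiovascular services before and after randomisation. It is not in the article, so a range is shown.

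**Formula.** Linear adjustment for one baseline covariate in a randomised comparison of two equal arms multiplies the variance of the estimated difference by 1 - r^2. The standard error and the interval width are multiplied by sqrt(1 - r^2). The equivalent arm size is 23,604 / (1 - r^2). The power column takes an effect that the unadjusted test would detect with 80% power (two-sided 5%).

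| Assumed r | 1 - r^2 | sqrt(1 - r^2) | Interval narrower by | Equivalent men per arm | Power instead of 80% |
|---|---|---|---|---|---|
| 0.2 | 0.96 | 0.980 | 2.0% | 24,588 | 81.6% |
| 0.3 | 0.91 | 0.954 | 4.6% | 25,939 | 83.6% |
| 0.4 | 0.84 | 0.917 | 8.3% | 28,100 | 86.4% |
| 0.5 | 0.75 | 0.866 | 13.4% | 31,472 | 89.9% |

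**What r might be.** A gamma-Poisson illustration, with every input assumed: mean 0.6 services in the two years before randomisation, mean 1.5 in the five years after, frailty variance V, half of it persistent. Then Var(before) = 0.6 + 0.36V, Var(after) = 1.5 + 2.25V and Cov = 0.5 × 0.6 × 1.5 × V = 0.45V.

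- V = 2: r = 0.9 / sqrt(1.32 × 6.0) = 0.32
- V = 4: r = 1.8 / sqrt(2.04 × 10.5) = 0.39
- V = 8: r = 3.6 / sqrt(3.48 × 19.5) = 0.44

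These correspond to intervals about 5% to 10% narrower. The result depends on the persistence assumption, because r is proportional to it. With one quarter persistent instead of half, r falls to 0.16 to 0.22 and the interval narrows by only about 1% to 2%.

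**Check by simulation.** Overdispersed counts were simulated at 23,604 per arm, 400 runs per scenario. The unadjusted comparison (Welch-type z) rejected a true null in 5.3% to 6.5% of runs, with a Monte Carlo standard error of about 1.1 points, which is compatible with 5%. The ratio of adjusted to unadjusted standard error was 0.86 to 0.94 for r from 0.50 to 0.35, as sqrt(1 - r^2) predicts.

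**The case against.** The strongest reply is that nothing here is wrong. An unadjusted comparison of two randomised arms of this size is unbiased, the simulation shows acceptable error rates, and the use of an optional covariate for one secondary outcome is partly a matter of preference. The size of the gain is also unknown, and if r is 0.3 or less the interval narrows by less than 5%. All of that stands. It limits the point to a suggested improvement, but does not remove it: the article fixes the test rather than leaving it to a later plan, and it names covariates for another outcome in the same paragraph.

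A reader might infer more than the article supports:

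- **That hospital costs are compared without adjustment.** The cost section names no covariate but excludes none, and an article may leave this to a fuller plan. Only the count comparison is fixed.
- **That each man's hospital history is already in hand.** The Randomization section says that patient data come from national registries; it does not say that earlier hospital contacts are extracted. That the registry holds them is a reasonable inference, not a documented fact. The gain is therefore cheap rather than free.
- **That skewness makes the t-test invalid.** Strong skewness is plausible for such counts but not documented, and at about 23,600 men per arm it did not distort the simulated test. For the cost ratios a nonparametric bootstrap is already planned.
- **That hospital-cost variance drives the cost-effectiveness result.** Programme, time and transport costs also enter, and the ratios depend on life years and QALYs, which this change leaves untouched.

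**Conclusion.** The point holds as an improvement in efficiency for one secondary outcome. The fixed t-test is valid but forgoes precision that a baseline covariate from the outcome's own registry could plausibly give. Over assumed r of 0.2 to 0.5 the interval would be about 2% to 13% narrower. At this sample size and near-equal allocation, the adjustment cannot lose appreciable precision.

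This rests on two things the article does not state: the value of r, and that the registry can supply earlier use for every man in both arms. Intention to treat is preserved, because the covariate is fixed before randomisation and recorded in the same way in both arms. The primary analysis, Cox regression for all-cause mortality, is not touched.

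**What to change.** Replace the t-test by a linear regression of the number of cardiovascular hospital services after randomisation on arm plus the man's own number of such services in a fixed window before randomisation, for example two years, with robust standard errors. The arm coefficient remains a difference in mean counts, so the quantity estimated does not change. Take the covariate from the registry only, not from the screening visit or questionnaire, so that it is defined alike for invited men and controls. Set the window and the list of cardiovascular contacts before outcome data are examined.

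For costs, state whether the hospital-cost difference is adjusted. If it is, the same covariate, or hospital cost before randomisation, can be included by refitting the regression within each bootstrap replicate.

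The cost is an earlier start date for the registry extract, a data-access request that covers the earlier window, and one more term in the model.

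### No invited-versus-control comparison of measured quality of life is stated; the only groups named for it split the invited arm after randomisation, and MANOVA suits the mortality in this trial poorly

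*Protocol article*

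**What the plan says.** The *Analysis of efficacy* section of the protocol article opens with a general rule: "Statistical analysis will be performed on an intention to treat basis". Mortality, first cardiovascular event and hospital services are then compared between the two groups.

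Quality of life is treated differently in the same paragraph: "Quality of life between controls, non-attenders, attenders without positive finding, and attenderswith AAA or PAD will be compared at baseline". That baseline comparison is made both unadjusted and with three covariates (age, marital status and other illness). The sentence continues with the longitudinal part: "prospective data from baseline, after 3, 5 and 10 years will be compared by MANOVA". That clause names no groups of its own and does not mention deaths or missing questionnaires.

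The *Outcome* section places quality of life among the secondary outcomes ("hospital services related to cardiovascular conditions and costs for such services, quality of life, and aneurismal progression") but omits it from its list of between-arm comparisons: "All-cause mortality, health care-related costs, cardiovascular and AAA-related mortality and cardiovascular hospital service are compared for the two groups".

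The *Analysis of cost-effectiveness* section does have a comparison by arm: "The net present values of costs, life years gained and QALYs gained will be compared between randomization groups". Its quality weights are a population norm for age and sex, with decrements from published work for men found to have, or treated for, cardiovascular disease.

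On data collection, the text after Figure 1 says that "enclosed with the invitation is a small questionnaire on smoking habits", and that this mailing includes the EQ-5D. *Follow-up and data collection* adds EQ-5D at visits and later controls of men with findings. Neither section describes how controls are surveyed.

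**The concern.** Attendance and screening result are known only after randomisation, and both depend on a man's health and behaviour. Men who stay away, men who come and are clear, and men who come and have disease differ from one another before screening can have affected them. The control group is not divided in this way: it contains would-be non-attenders and men with undetected AAA or PAD. A lower score in men with a finding could therefore reflect the disease, the label or selection, and the comparison cannot tell these apart. The covariate adjustment is attached to the baseline comparison and would not restore the randomised comparison in any case.

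A screening programme can affect quality of life through reassurance, worry or treatment. The article says the trial is meant to inform policy on a national programme, so the effect of being invited is the question that matters. As described, the analysis would mainly show that sicker men score lower. If only men with complete series are kept, it would show this among survivors.

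**Working it through.** The documents give no sample size, standard deviation or target difference for quality of life, so there is no stated figure to reproduce. The check sets the passages side by side and sizes the consequence from the inputs in *Power and expected benefit*.

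**1. Which comparisons are as randomised?**
- Mortality, first cardiovascular event, hospital services and costs: two arms.
- QALYs: two arms, but with assumed weights. Any quality-of-life effect of invitation is an input there and is not estimated from the trial's EQ-5D.
- Measured quality of life: four groups named, three of them inside the invited arm. No two-arm comparison appears anywhere.

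**2. Size of the groups.** Inputs: about 50,000 men, nominally half invited; attendance 75%; prevalence 4% (AAA) and 8% (PAD), 12% together if they do not overlap (assumption).
- Invited: 50,000 / 2 = 25,000
- Attenders: 25,000 × 0.75 = 18,750; non-attenders: 6,250
- Attenders with a finding: 18,750 × 0.12 = 2,250; without: 16,500

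If every AAA case also had PAD, the prevalence would be 8% and the group with a finding 18,750 × 0.08 = 1,500. Each of the three parts is set against about 25,000 unselected controls.

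**3. Who could remain in a four-point MANOVA?** The upper bound on complete series is 1 − cumulative mortality, before any non-response. Inputs: five-year mortality 28% with AAA or PAD and 15% in controls; ten-year mortality in controls 36%, which the article introduces conditionally.
- Controls, 5 years: 1 − 0.15 = 85%
- AAA or PAD, 5 years: 1 − 0.28 = 72% (2,250 × 0.72 = 1,620)
- Controls, 10 years: 1 − 0.36 = 64% (25,000 × 0.36 = 9,000 lost)

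The 28% carries no benefit from screening. Crediting the plan's own drug effect (20% reduction in one-third of men) gives 0.28 × (1 − 0.20/3) = 26.1%, leaving about 74%. Suppose the assumed halving of AAA-related death is also credited, read as 0.5 points of all screened men and falling wholly on the 12% with a finding (0.5/0.12 = 4.2 points). Mortality is then about 22%, leaving 78%. The loss stays unequal to the controls' 85%.

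Ten-year mortality with AAA or PAD is not given. Three assumptions, each without screening benefit:

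| Assumption | Calculation | Mortality | Left | Of 2,250 |
|---|---|---|---|---|
| Constant hazard | 1 − 0.72² | 48% | 52% | 1,166 |
| Constant hazard ratio, ln 0.72 / ln 0.85 = 2.02 | 1 − 0.64^2.02 | 59% | 41% | 913 |
| Constant risk ratio, 0.28/0.15 | 0.36 × 0.28/0.15 | 67% | 33% | 738 |

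The constant-hazard row is probably too mild. Applied to controls, it gives 1 − 0.85² = 28% at ten years, whereas the article assumes 36%.

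**The case against.** The strongest reply has four parts.

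- **The text does not specify a complete-case analysis.** A reader might infer that the plan analyses complete series only and drops everyone who dies. The article says neither. Exclusion follows from standard MANOVA, but deaths could be given a value or missing data imputed, and a full protocol or analysis plan that is not shown may say so. Even under standard MANOVA, men who die after year 10 would be kept, and a look at 3 or 5 years loses only earlier deaths. This part stands, so the retention figures are conditional.
- **The four groups are tied grammatically to the baseline comparison.** The MANOVA clause names none, so carrying the four groups over is plausible but not certain. This also stands. It leaves the longitudinal groups undefined, however, and the *Outcome* section does not supply a two-arm comparison. Comparing quality of life by screening result is a legitimate descriptive question.
- **QALYs are compared by arm, and that comparison takes account of deaths.** This is true and should be acknowledged. It does not answer the point, because the weights are not the trial's measurements.
- **Nothing shows that controls lack EQ-5D data.** A reader might infer this because the questionnaire is described only with the invitation and at visits. The article is merely silent, and it names controls as a measured group at baseline, which implies some collection. The stronger inference is not supported.

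**Conclusion.** The concern holds in limited form. The article states intention to treat without exception, names only a post-randomisation grouping for measured quality of life, and states no comparison of it by arm. That conclusion rests on the text alone.

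The choice of MANOVA makes matters worse if it is applied in its standard form. Deaths alone would then leave at most 85% of controls against about 72% of men with AAA or PAD at five years, and at most 64% against 33% to 52% at ten. The ten-year range for AAA or PAD is an assumption, and the five-year 72% would rise to between 74% and 78% if the plan's own assumed benefits were credited. Non-response would lower all these figures.

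The point concerns a secondary outcome. It does not touch the mortality comparisons, which are stated by arm, and it is no ground for saying that the trial as a whole departs from intention to treat.

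**What to change.** - Make invited versus control, as randomised, the main comparison of measured quality of life. Use a likelihood-based repeated-measures model on every available EQ-5D measurement in place of MANOVA.
- Add a supporting analysis that handles death explicitly, for example with EQ-5D set to 0 from death onward. The model's missing-at-random assumption does not by itself resolve death, so this analysis is needed.
- Keep the four-group comparison, labelled descriptive and non-randomised.
- State whether EQ-5D is collected from controls at follow-up. If it is not, state that no randomised conclusion on measured quality of life will be drawn.

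The cost is a change of wording and slightly more analysis work. A new mailing to controls, if none is planned, would be a real expense. The fix does not depend on it, because the last step covers that case.
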